## 3.6. Sample size

The target sample size is 300 participants. The allocation ratio will be 2:1, with 200 participants in the elderly experimental group (aged 60–80) and 100 participants in the younger control group (aged 18–59).

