### 3.10.2. Statistical methods

**Principles of statistical analysis:**

All statistical analyses were performed using IBM SPSS (version 26).

Demographic analysis will be performed in FAS population, the primary analysis (safety) will be performed in the SS population, and the secondary analysis (immunogenicity) will be performed both in the FAS and PPS population.

The Kolmogorov-Smirnov test was used to evaluate the distribution types. Non-normally distributed and ordered data are represented by the median (range). Measurement of pseudovirus 50% neutralization titers (pVNT_50_s) are represented by geometric means. Pearson’s chi-square test, continuity correction, and Fisher’s exact test were used to check the proportion of the count data.

The Mann-Whitney U test and paired t-test were used to compare differences between groups, the Wilcoxon rank-sum test was used to compare intragroup differences, and the nest t-test was used to compare unmatched groups. We displayed the median values of each group in the figures using GraphPad Prism 8 and estimated the differences based on the 95% confidence interval (CI).

Baseline characteristics were screened using univariate logistic regression, and the significantly different factors (*P*_value<0.1) were further analyzed using multivariate logistic regression. The analysis results are presented using an OR combined with a 95% CI (lower–upper) in the table.

In correlation analysis, the Pearson correlation test was used to process normally distributed datasets, while the Spearman rank correlation test was used to process non-normally distributed datasets. An absolute R value>0.5 indicated a strong correlation, whereas an absolute R value≤0.5 indicated a weak correlation.

The hypothesis test was bilateral, and a *P*_value<0.05 was considered statistically significant.

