**Breakthrough infection analysis:**

The population for breakthrough infection analysis will be based on the FAS population and exclude participants whose SARS-CoV-2 infection status during the end of the 2022 pandemic cannot be confirmed through follow-up. The **Demographic analysis** will be performed as above.

(1) Proportion of different breakthrough infection states

Based on follow-up data, the status of breakthrough infections among the participants will be statistically described, and the infection rate will be used as an intergroup categorical variable for comparison using Pearson’s chi-square test.

(2) Proportion of different types of breakthrough infection symptoms

The symptoms of symptomatic infected individuals will be statistically described and displayed as intergroup categorical variables.

(3) Duration of breakthrough infection symptoms (days)

The duration of symptoms will be statistically described using the duration as the classification criterion (if longer than 7 days) and compared as an intergroup classification variable.

(4) Correlation between infection and antibody titers

The infection status within the two groups will be statistically described, and the corresponding antibody titers will be presented as continuous variables. An intragroup comparison will be performed using the Mann–Whitney U test, and the corresponding medians and 95% CIs will be calculated.

(5) Correlation between symptom severity and antibody titers

Based on the classification criteria of whether the duration of symptoms is longer than 7 days, whether there is accompanying fever, and whether there are multisystemic symptoms, the infection symptoms of the two groups will be statistically described. The corresponding antibody titers will be considered continuous variables; the Mann–Whitney U test will be employed for the intragroup comparison, and the corresponding medians and 95% CIs will be determined .

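### Titre against infection and against symptom severity is tested only within each age group; with no age-stratified analysis across both groups, power is lost and the two p-values can differ by chance

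*Protocol*

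**What the plan says.** The protocol, section 3.10.2, Breakthrough infection analysis, item (4), relates antibody titre to infection status: "An intragroup comparison will be performed using the" Mann–Whitney U test, with medians and 95% CIs. Item (5) relates titre to three severity splits (symptoms beyond 7 days, fever, multisystemic symptoms), and again "the Mann–Whitney U test will be employed for the intragroup comparison". The groups are the two age groups, planned in section 3.6 "with 200 participants in the elderly experimental group (aged 60–80) and 100 participants in the younger control group (aged 18–59". The analysis starts from the FAS and will "exclude participants whose SARS-CoV-2 infection status during the end of the 2022 pandemic cannot be confirmed through follow-up", so 200 and 100 are upper bounds.

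The general principles in section 3.10.2 make tests two-sided ("The hypothesis test was bilateral") with a P "value<0.05 was considered statistically significant". They also describe univariate then multivariate logistic regression, but only to screen baseline characteristics; no outcome is named and titre is not mentioned. The protocol nowhere specifies a combined, age-stratified or interaction analysis of titre against infection or severity. It states no infection rate, effect size or power for these items.

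**The concern.** Items (4) and (5) ask whether titre goes with infection and with symptom severity. Splitting the participants by age and testing each part alone answers this with at most 200 people in one test and at most 100 in the other. If the association is similar in both groups, each test discards information held by the other. A real association may then be missed in the young, or in both groups.

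The second risk concerns reading. The trial is built around an elderly and a young group, and items (4) and (5) would give one p-value for each. With unequal group sizes, the same true association is more likely to reach significance in the elderly. A result significant in one group only could be taken to mean that titre matters at one age and not the other, when it reflects sample size and chance.

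**Working it through.** There is no stated power or agreement figure to reproduce: section 3.6 gives 300 participants without an effect size, event rate or power.

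**Inputs from the protocol.** 200 elderly and 100 young (section 3.6); two-sided alpha 0.05; Mann–Whitney within each age group (section 3.10.2).

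**Inputs assumed.** The shift d in log titre between infected and uninfected is the same in both groups, from 0.2 to 0.8 SD. The infected share p is the same in both groups, from 50% to 90%. Log titres are normal. All 200 and 100 are analysable unless stated.

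**Formula.** Large-sample power of the rank test is Φ(λ − 1.96) + Φ(−λ − 1.96), with λ = d × √[n p (1 − p) × 3/π]. An age-stratified (van Elteren) test uses the summed information, n = 300. Disagreement (exactly one group significant) is P_E(1 − P_Y) + P_Y(1 − P_E).

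**Worked case, d = 0.4, p = 0.8.**
- Elderly: 200 × 0.16 × 0.955 = 30.56; λ = 0.4 × 5.53 = 2.21; power 60%.
- Young: 100 × 0.16 × 0.955 = 15.28; λ = 0.4 × 3.91 = 1.56; power 35%.
- Stratified: 300 × 0.16 × 0.955 = 45.84; λ = 0.4 × 6.77 = 2.71; power 77%.
- Elderly only: 0.599 × 0.654 = 39%. Young only: 0.346 × 0.401 = 14%. Disagreement 53%. Neither: 0.401 × 0.654 = 26%.

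**Range at 200 and 100.** Each cell gives power in elderly / young / stratified, then disagreement.

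| d (SD) | 50% infected | 80% infected | 90% infected |
|---|---|---|---|
| 0.2 | 28 / 17 / 40; 35% | 20 / 12 / 27; 27% | 13 / 9 / 17; 20% |
| 0.3 | 55 / 31 / 72; 52% | 38 / 22 / 53; 43% | 24 / 14 / 33; 31% |
| 0.4 | 79 / 50 / 92; 50% | 60 / 35 / 77; 53% | 38 / 22 / 53; 43% |
| 0.5 | 93 / 69 / 99; 34% | 79 / 50 / 92; 50% | 55 / 31 / 72; 52% |
| 0.6 | 99 / 83 / >99; 18% | 91 / 65 / 98; 38% | 70 / 42 / 86; 53% |
| 0.8 | >99 / 97 / >99; 3% | 99 / 88 / >99; 13% | 91 / 65 / 98; 38% |

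Disagreement peaks at about 54% and is at least 40% while elderly power lies between about 34% and 90%. The elderly-only pattern peaks at about 41%. A simulation of 4,000 trials per setting agrees: at 80% infected and 0.42 SD it gave 62%, 36% and 79% power, with 54% disagreement.

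**Fewer analysable participants.** At d = 0.4 and p = 0.8, 160 and 80 give 51 / 29 / 68 with 50% disagreement; 120 and 60 give 40 / 23 / 56 with 45%.

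**Item (5).** Assume 160 and 80 infected, 30% of them with the worse symptom class. A 0.3 SD shift gives 40 / 23 / 55 with 44% disagreement; 0.5 SD gives 81 / 52 / 93 with 49%; 0.8 SD gives 11% disagreement.

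**Power of an age-difference test.** At 80% infected, the standard error of the difference between the two shifts is √(1/160 + 1/40 + 1/80 + 1/20) = 0.306 SD. For 0.4 SD in one group and none in the other, 0.4/0.306 = 1.31, so power is about 26%.

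The general principles assign the Wilcoxon rank-sum test to intragroup comparisons, while items (4) and (5) name Mann–Whitney. For two independent samples these are the same test, so no figure changes.

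**The case against.** Keeping the age groups apart is defensible. Age may drive both titre and infection, and a pooled test that ignored age would be worse. The stated objective concerns the elderly, and the elderly-only test speaks to them directly. Medians with confidence intervals are also planned, so the output is more than two verdicts. Breakthrough infection is neither a primary nor a secondary endpoint. All of this stands. It supports conditioning on age, which a stratified test also does, and it lowers the priority.

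Three stronger readings are tempting, and the protocol does not support them.
- A reader might infer that the two verdicts will disagree about half the time whatever the truth. That holds only for moderate effects, and the protocol fixes neither the effect nor the infection rate.
- A reader might infer that significance in the elderly alone is the result to expect. It is frequent but never a majority; at 0.4 SD and 90% infected the commonest outcome is that neither test is significant (0.62 × 0.78 = 48%).
- A reader might infer that the protocol plans to claim an age difference from the two p-values. Neither item says so or asks whether the association depends on age.

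The power gain also depends on the association being similar in the two groups.

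**Conclusion.** The point holds as a limited one. Items (4) and (5) fix a within-group test as their only inference. When the association is similar at both ages, this gives up power that an age-stratified test on the same data would recover. In the worked case the loss is about 17 points against the elderly test (77 − 60) and about 42 against the young test (77 − 35); for large effects it fades.

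Different verdicts in the two age groups are common under an identical association of moderate size and uncommon under a large one. The pair of p-values is therefore no evidence of an age difference. These sizes rest on assumed effects, infection shares, normal log titres and full group sizes. The analysis is supplementary, so priority is low to moderate.

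**What to change.** For each outcome in items (4) and (5), add one age-stratified analysis across both groups and make it the main result. This can be a van Elteren test stratified by age group, or logistic regression of the outcome on log2 titre with age group as a term, reporting the odds ratio per two-fold titre with its 95% CI. Keep the within-group medians, intervals and tests as supporting description.

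State that any claim that the association differs by age rests on the titre-by-age-group estimate and its CI, not on comparing the two p-values. State also that this estimate has low power (about 26% in the case above), so a non-significant interaction does not show that the associations are equal.

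Cost: a change of wording and a little more analysis; no new participants, visits or assays. The logistic model assumes a log-linear relation, which the stratified rank test avoids. If the associations differ strongly between the age groups, the power gain shrinks or disappears.

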**Pseudovirus neutralization test analysis**

Based on the FAS population, an equal number of participants were randomly selected from both groups, ensuring no significant intergroup differences in gender and age, and no missing values at baseline and follow-up points at the 2^nd^, 7^th^, 8^th^, 13^th^, and 16^th^ months. The analysis of antibody-positive rates and titers (pVNT_50_s) is in the same way as the **Secondary analysis** mentioned above.

(1) Correlation between pVNT_50_s and symptoms

The infection status within the two groups will be statistically described, and the corresponding pVNT_50_s will be treated as continuous variables. An intergroup comparison will be performed using the nested t-test, and the corresponding geometric means and 95% CIs will be provided.

(2) Correlations between wild-type SARS-CoV-2–specific pVNT_50_s and variant-specific pVNT_50_s

The pVNT_50_s measured at each follow-up point will be statistically described as continuous variables. The Kolmogorov–Smirnov test will be utilized to evaluate data normality, followed by the Pearson correlation test or the Spearman rank correlation test for correlation analysis.

(3) Correlations between different variant-specific pVNT_50_s

The pVNT_50_s measured at each follow-up point will be statistically described as continuous variables. The Kolmogorov–Smirnov test will be employed to evaluate data normality, followed by the Pearson correlation test or the Spearman rank correlation test for correlation analysis.

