## 2.3. Trial design

This trial is investigator-initiated and adheres to the principles of good clinical practice. It is a multi-center, prospective, single-arm clinical study. The trial will include two participant groups: an elderly group aged 60 to 80 years and a younger control group aged 18 to 59 years.

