## 3.2. Eligibility criteria

### 3.2.1. Inclusion criteria

1. Signed informed consent;
2. In females, the urine pregnancy test was negative;
3. At least 6 months of follow-up was completed;
4. HBsAg, anti-HCV, HIV, treponema pallidum hemagglutination assay (TPHA) screening was negative;
5. Armpit temperature was ≤37.0℃;
6. The young group was aged 18–59 years, and the elderly group between 60–80 years.

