## 3.8. Allocation and vaccine management

### 3.8.1. Allocation

The participants will be assigned to either the experimental or control group in a 2:1 ratio based on age.

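### The pseudovirus subset must show no significant age difference between two groups defined by non-overlapping ages, which random selection cannot achieve at any useful size

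*Protocol*

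**What the plan says.** Protocol section 2.3 sets up two groups: "an elderly group aged 60 to 80 years and a younger control group aged 18 to 59 years". Section 3.2.1 repeats the bands as an eligibility criterion ("The young group was aged 18–59 years, and the elderly group between 60–80 years"), section 3.6 gives the targets of 200 elderly and 100 young with the same bands, and section 3.8.1 has participants "assigned to either the experimental or control group in a 2:1 ratio based on age".

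Section 3.10.2, under the pseudovirus neutralization test analysis, draws a subset from the full analysis set (FAS). It says "an equal number of participants were randomly selected from both groups, ensuring no significant intergroup differences in gender and age", and it also requires "no missing values at baseline and follow-up points at the 2^nd^, 7^th^, 8^th^, 13^th^, and 16^th^ months". No size is given for the subset and no test is named for the age comparison.

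The general principles in the same section say "The hypothesis test was bilateral" and "a *P*_value<0.05 was considered statistically significant". They list the Mann-Whitney U test among the methods for comparing groups. Section 3.10.1 already removes from the FAS anyone who did not receive all three doses.

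**The concern.** The selection rule asks for balance on the variable that creates the groups. The bands 18–59 and 60–80 do not overlap, so no draw can make the groups alike in age. Only two outcomes are open. Either the age condition is quietly ignored, and the subset was not chosen as the protocol says, or the choice is steered towards people on either side of the 59/60 boundary, which gives up random selection and most of the age contrast that the trial was set up to study.

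Several results depend on this subset: the antibody-positive rates and pVNT50 titres in the two groups, the relation of pVNT50 to symptoms, and the correlations between wild-type and variant-specific titres and among variants. A reader of those results needs to know whom the subset represents.

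The completeness condition narrows it further, to three-dose recipients with values up to month 16. That restriction is stated openly and contradicts nothing, but it limits how far the results carry.

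**Working it through.** The protocol gives no subset size or balance figure, so there is nothing to reproduce. The check asks how large a subset could be and still meet the age condition.

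**Inputs.** Age bands 18–59 and 60–80 (sections 2.3, 3.2.1, 3.6); equal numbers n per group (section 3.10.2, pseudovirus analysis); two-sided test at 0.05 (section 3.10.2, principles). The test for age is not named, so several were tried.

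**Exact Mann-Whitney.** Every elderly age exceeds every young age, so U = 0 whichever people are drawn. Of the C(2n,n) equally likely arrangements, only two are this extreme, one in each direction. Hence P = 2/C(2n,n):

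- n = 3: 2/20 = 0.10
- n = 4: 2/70 = 0.029
- n = 5: 2/252 = 0.008

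The largest n with P ≥ 0.05 is 3. The exact two-sample Kolmogorov-Smirnov test gives the same values at these sizes.

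**Asymptotic Mann-Whitney.** With continuity correction P is 0.081 at n = 3 and 0.030 at n = 4, so the limit is again 3. Without correction P is 0.0495 at n = 3, and the limit falls to 2.

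**Unpaired t-test, random draws.** Assume ages uniform within each band (an assumption; the protocol gives no age distribution). In 20,000 simulated draws per n, the share with P ≥ 0.05 was about 14% at n = 3, 0.9% at n = 4 and 0.02% at n = 5, and no draw passed at n = 6 or at any larger size tried (up to 30). The Welch version gave 33%, 3.8% and 0.2%, and again none from n = 6.

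For scale at n = 20: the mean difference is 70 − 38.5 = 31.5 years, the SDs are 41/√12 = 11.8 and 20/√12 = 5.8, and t = 31.5/√(11.8²/20 + 5.8²/20) ≈ 10.7.

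Drawing only from ages 50–59 and 60–65 does not help: 11% passed at n = 3, 0.6% at n = 4 and none from n = 5.

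**Unpaired t-test, contrived ages.** Take one young person aged 18, all other young aged 59, and all elderly aged 60. The mean difference is 1 + 41/n and its standard error is 41/n, so t = 1 + n/41. At n = 40, t = 1.98 and P = 0.052, the largest n that passed in the configurations searched. The median ages are then 59 and 60.

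**Completeness.** The protocol schedules nine antibody time points: baseline and months 1, 2, 4, 7, 8, 10, 13 and 16. The subset rule requires six of them: baseline and months 2, 7, 8, 13 and 16.

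**The case against.** The best defence is that the sentence was meant differently: each subset should resemble its own parent group in age, or balance was intended within age groups. The text does not support this. The condition is on intergroup differences, and elsewhere in section 3.10.2 that word means elderly against young, with intragroup used for the other case. If another meaning was intended, the sentence still needs rewriting.

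Other parts of the defence stand, and they rule out stronger readings that a reader might infer:

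- *Three per group is an absolute ceiling.* It is the limit for the exact Mann-Whitney test. No test is named for age, the uncorrected asymptotic version gives 2, and a t-test can be kept non-significant at larger sizes with contrived ages.
- *The subset was hand-picked, or redrawn until a test passed.* The protocol describes random selection and no repeated drawing. The gender condition can be met without any such device.
- *Only people who attended every visit qualify.* Months 1, 4 and 10 may be missing.
- *All variant-specific results come from this subset alone.* The secondary analysis in section 3.10.2 places variant-specific titres in the FAS and per-protocol analyses. The subset may in practice be their source, but the protocol does not say so.

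It is also fair that the primary endpoint is safety, analysed in the safety set, and that the secondary titre analyses are planned on the FAS and per-protocol set. This selection rule does not touch the choice of those sets.

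**Conclusion.** The age condition is wrong as written. It conflicts with the definition of the groups, and random selection cannot meet it at any useful subset size. Under the exact Mann-Whitney test at two-sided 0.05, 4 or more per group fails whatever ages are drawn. Under a t-test with ages uniform in each band, a random draw of 6 or more per group has practically no chance of passing. The first result rests only on the age bands and the choice of test; the second also rests on the assumed age distribution.

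The gender condition is feasible and is not in question. The completeness condition is a limit on generalisation, not a contradiction. How much it matters cannot be judged from the protocol, which does not say how many participants have all six values or whether that differs by age group.

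Because this is a non-primary subset analysis, it is something that should be fixed, not a fault that undermines the trial's main conclusions.

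**What to change.** 1. Delete age from the between-group balance condition.
2. State that participants are drawn at random within each age group, with sex balanced by stratifying the draw rather than by requiring a non-significant test.
3. The protocol describes the selection in the past tense. If it has already been done, state how it was actually done, including what was done about age.
4. Compare the subset with the rest of the FAS, within each age group, on baseline characteristics. Limit its conclusions to three-dose recipients with values at baseline and months 2, 7, 8, 13 and 16.

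The cost is a change of wording and a little extra descriptive tabulation. The age difference between the two subsets remains, as the design intends. Choices such as stratifying by site or using a different longitudinal model are matters of preference and are not needed to remove the contradiction.

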## 3.11. Safety/harms

AEs and SAEs will be monitored and recorded from the time the participant signed the informed consent form to the completion of the follow-ups. AEs/SAEs will be recorded in detail, including onset date, duration, severity, treatment, and relation to the investigational medical product. All AEs/SAEs will be followed up until finalized (recovery/relief, stability, death, or other explainable circumstances, such as lost to follow-up).

Once identified, SAEs must be acted upon and reported within 24 hours. They will be reported to the Institutional Review Board (IRB) as soon as possible.

## 3.12. Auditing

1. All research centers participating in clinical trials should adopt standard operating procedures to ensure the implementation of quality control and quality assurance systems for clinical trials;
2. To ensure the quality of the multi-center trial, before starting the formal trial, the principal investigators of each study site shall jointly discuss and formulate the protocol, and the relevant investigators shall be trained at the same time;
3. Each study site shall implement the trial according to a unified protocol;
4. Each study site will implement the same procedure to manage the trial vaccines, and the experimental vaccine manager must carefully store vaccines in accordance with the storage conditions proposed by the unit leader.
5. All observed results and abnormal findings in the clinical trials should be carefully verified and recorded in a timely manner to ensure the reliability of the data. All kinds of instruments, equipment, reagents, and standards used in the clinical trials must meet strict quality standards and function correctly under normal conditions. The recording and transfer of clinical data must be carried out by experienced investigators and supervised or verified to ensure data accuracy and scientific integrity. Clinical trial conclusions must be derived from the raw data.
6. The investigators in charge of the study should fill in the research medical records and CRF on time, completely, in detail, and accurately and submit or store documents according to the prescribed procedures after being signed and confirmed by a superior; all data related to the study must be centrally managed and analyzed.
7. To ensure the reliability and completeness of the trial data, the principal investigators of each study site, clinical research partners, and supervisors will monitor their clinical systems regularly to judge whether the implementation of the trial is consistent with the protocol and whether the reported data are consistent with the records of the study sites. A report will follow every visit.

